## Biomarker Testing (Applicable Only to Leukemia Patients)

### Biomarker

- Acetylation Levels of Histones H3 and H4

### Sample Collection Timing

Single-Dose Administration Phase: Blood samples of 4 mL will be collected within 0.5 hours before administration, and at 1 hour, 4 hours, 24 hours, and 48 hours after administration.

Multiple-Dose Administration Phase:

D8: Blood samples of 4 mL will be collected at 0.5 hours before administration, and at 1 hour, 4 hours, and 24 hours after administration.

D11: Blood samples of 4 mL will be collected at 0.5 hours before administration and at 1 hour after administration.

D15: Blood samples of 4 mL will be collected at 0.5 hours before administration, and at 1 hour, 4 hours, 24 hours, 48 hours, and 72 hours after administration.

### Sample Handling, Testing, and Storage

Anticoagulant: K_2_EDTA

For each blood collection, 4 mL of peripheral blood will be placed in an anticoagulant collection tube. Peripheral blood mononuclear cells (PBMCs) will be isolated using red blood cell lysis buffer or the Ficoll-Paque method. The isolated PBMCs will be lysed and prepared as samples according to the protocol for Western Blot analysis. The acetylation levels of histones H3 and H4 will be detected using the Western Blot method. Samples will be stored in a freezer at -70 ± 10°C.

Quantitative Analysis Method:

In the single-dose administration phase, the acetylation levels of histones will be referenced to the baseline (Baseline) established from the sample collected 0.5 hours before administration on D1. The results of all time point samples will be quantified, and the trends in histone acetylation levels at each time point will be analyzed. In the multiple-dose administration phase, the acetylation levels of histones will be referenced to the baseline (Baseline) established from the sample collected 0.5 hours before administration on D5. The results of all time point samples will be quantified, and the trends in histone acetylation levels at each time point will be analyzed.

## Sampling Time Window

For sampling intervals of less than or equal to 1 hour, the allowable error must be within ±5% of the previous time point interval. For sampling intervals greater than 1 hour, the allowable error must be within ±2.5% of the previous time point interval. Any deviations from the permitted sampling time range must be immediately documented in the relevant original data forms.

Table 9 Sampling Time Window

| Time Points (Post-Administration) | Time Window |
| --- | --- |
| 10min | ±1min |
| 20min | ±1min |
| 30min | ±1min |
| 35min | ±1min |
| 45min | ±1min |
| 1h | ±1min |
| 2h | ±2min |
| 4h | ±3min |
| 6h | ±3min |
| 8h | ±3min |
| 10h | ±3min |
| 24h | ±21min |
| 48h | ±36min |
| 72h | ±48min |

## Efficacy Evaluation

- Objective Response Rate (ORR): Defined as the proportion of patients whose tumor volume has decreased to a predetermined value and maintained for a minimum required duration. ORR is generally defined as the sum of complete response (CR) and partial response (PR).
- Progression-Free Survival (PFS): The time from the start of patient enrollment until the occurrence of objective tumor progression or death.
- Disease Control Rate (DCR): Refers to the proportion of patients whose tumors have either decreased or stabilized for a certain period, including cases of complete response (CR), partial response (PR), and stable disease (SD).

The efficacy evaluation correspondence for this trial is referenced in the table below. For other diseases not specified in the table, the investigator will determine efficacy based on the latest evaluation criteria for that disease:

| Disease Names | Efficacy Evaluation Criteria |
| --- | --- |
| B-cell Lymphoma  T-cell Lymphoma | ORR =CR+PR+MR  DCR= CR+PR+MR+SD |
| Multiple Myeloma | ORR =sCR+CR+VGPR+PR+MR |
| B-cell Acute Lymphoblastic Leukemia  T-cell Acute Lymphoblastic Leukemia | ORR= CR+CRi  This disease is not applicable for DCR analysis. |
| Other Relapsed or Refractory Hematologic Malignancies | For diseases not defined in this trial, the determination will be based on the clinical researcher's judgment according to the efficacy evaluation guidelines for each disease. |

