| **Drug Administration Plan** | The dosing phase of this study includes three stages: the single-dose phase, the multiple-dose phase, and the extended dosing phase. The pharmacokinetics of the single-dose and multiple-dose administrations are combined, during which safety, tolerability, and preliminary efficacy are observed.  **1. Single-Dose Phase**  The single-dose escalation phase will begin with the starting dose and proceed in an ascending order from low to high doses, with 3 to 6 subjects enrolled in each dose group. In each dose group, 3 subjects will be enrolled sequentially, and a single dose will be administered on Day 1 (D1) at that dose, followed by a 6-day observation period (D2-D7). Each subject will receive treatment with a single dose.  **2. Multiple-Dose Phase**  After completing the pharmacokinetic blood sampling for the single-dose administration, if the subject is well-tolerated, they will enter the multiple-dose phase, with doses administered on Days 8, 11, and 15. Each subject will receive the same dose as in the single-dose phase, with the dose-limiting toxicity (DLT) observation period defined as the first administration to 25 days after the first dose. Initially, only one subject will be enrolled in each dose group to observe their tolerability and safety within the 25 days following the first dose. Only if this subject does not experience a DLT will the remaining two subjects in the same dose group be allowed to enroll simultaneously.  If none of the 3 subjects in a dose group experience DLT, the trial will proceed to the next dose group. If 1 out of the 3 subjects in a dose group experiences DLT, an additional 3 subjects will be recruited to receive the same dose of the investigational drug, and they will be monitored for DLT occurrence.  If 1 DLT occurs among the 6 subjects, the trial will proceed to the next dose group. If 2 or more DLTs occur among the 3 subjects, or if 2 or more DLTs occur among the 6 subjects, the trial will be reduced to the previous dose group. If the previous dose group has fewer than 6 evaluable subjects, an additional 3 subjects will be enrolled to bring the total number of evaluable subjects to 6. If no more than 1 DLT occurs among the 6 evaluable subjects, the trial will be halted, and that dose group will be declared as the maximum tolerated dose (MTD). If the previous dose group has already reached 6 evaluable subjects, the trial will be halted, and that dose will be declared as the MTD.  During the multiple-dose escalation trial, real-time analysis of the pharmacokinetic (PK) data for the selected dose groups will be conducted to determine whether the drug reaches a saturation state in the body based on PK and pharmacodynamic (PD) indicators.  **3. Extended Treatment Phase**  After completing the single-dose and multiple-dose phases, if the efficacy assessment indicates clinical benefit for the subject, they will enter the extended dosing phase. In the extended dosing phase, treatment may continue according to the original dosing regimen or with adjustments to the dose based on the subject's tolerability and existing clinical results. Each dosing cycle lasts 21 days, with doses administered on Days 1, 4, 8, and 11 of each cycle. The number of extended dosing cycles will vary based on the patient's efficacy; subjects who achieve an objective response rate of partial response (PR) or higher after 6 cycles may continue receiving the treatment until disease progression, while those who do not reach PR will discontinue the treatment. Efficacy and safety data will continue to be collected during the extended dosing phase. |

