Imaging studies: CT, PET-CT, or whole-body X-ray examinations. Results from screenings conducted within 4 weeks prior do not need to be repeated. During the continuation dosing phase, imaging should be performed once every 2 dosing cycles. If the dosing phase is extended, imaging should occur before the next cycle after the 2nd, 4th, 6th, etc. dosing cycles, with the imaging methods used for evaluating efficacy remaining consistent with the baseline. The examination window is ±3 days. For subjects with leukemia, the primary efficacy evaluation is based on bone marrow smears, and the investigator will determine whether imaging studies are necessary based on clinical circumstances.

Whole-body X-rays include views of the skull, pelvis, femur, humerus, thoracic spine, lumbar spine, and cervical spine.

1. Echocardiography is not a routine examination. It should be performed if the subject experiences symptoms such as precordial pain or palpitations, or if deemed necessary by the investigator.
2. Efficacy assessment: During the continuation dosing phase, for subjects who first achieve disease remission (CR/PR) after the 2nd, 4th, 6th, etc. dosing cycles, efficacy confirmation should be conducted 4 weeks after the initial efficacy assessment.
3. M protein testing is conducted only for patients with multiple myeloma and includes: (1) serum protein electrophoresis (Albumin, Alpha 1, Alpha 2, Beta 1, Beta 2, Gamma, M-spike); (2) immunofixation electrophoresis (IgG, IgA, IgM, light chain types); (3) β2-MG; (4) quantitative serum immunoglobulins (serum IgG, serum IgA, serum IgM, serum kappa light chains, serum lambda light chains, and the kappa/lambda ratio);
4. M protein testing is conducted only at the start of each cycle beginning with the 2nd cycle during the extended dosing phase;
5. Bone marrow examination includes: results from examinations conducted within 4 weeks prior to screening do not need to be repeated. The procedures include: (1) classification of bone marrow cytology smears; (2) bone marrow biopsy with immunohistochemistry; (3) flow cytometry. For leukemia patients, the bone marrow examination is limited to bone marrow smears and flow cytometry;

- The frequency of bone marrow cytology smear classification, bone marrow biopsy with immunohistochemistry, and flow cytometry at the end of multiple dosing and during the extended treatment phase will be determined based on clinical needs.

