## Criteria for the Evaluation of Multiple Myeloma

"Chinese Guidelines for the Diagnosis and Treatment of Multiple Myeloma (Revised in 2017)" and the 2016 International Myeloma Working Group (IMWG)

| **IMWG Response Criteria** | |
| --- | --- |
| **sCR** | The following definition of complete response includes a normal free light chain (FLC) ratio, and a bone marrow biopsy (after calculating ≥100 plasma cells) showing no clonal cells based on immunohistochemical examination (with κ and λ ratios of ≤4:1 or ≥1:2 for the patient). |
| **CR** | Serum and urine immunofixation electrophoresis negative, with no evidence of any soft tissue plasmacytomas, and plasma cells in the bone marrow aspirate <5%. |
| **VGPR** | Immunofixation electrophoresis may detect serum and urine M proteins, but electrophoresis is negative or serum M protein is reduced by ≥90% with urine M protein levels. |
| **PR** | - Serum M protein decreased by ≥50% and 24-hour urine M protein decreased by ≥90% or reached <200 mg/24 h. - If serum and urine M protein cannot be measured, a difference of ≥50% in free light chain (FLC) levels between the affected and unaffected areas can be used as a substitute for the M protein criteria. - If serum and urine M protein testing and serum free light chain testing cannot be performed, plasma cells must be reduced by ≥50% to substitute for the M protein criteria, provided that the baseline percentage of plasma cells in the bone marrow is ≥30%. In addition to these criteria, if present at baseline, the size of soft tissue plasmacytomas (the sum of the products of the maximum vertical diameters of multiple measurable lesions [SPD]) must decrease by ≥50%. |
| **MR** | Serum M protein decreased by ≥25% but ≤49%, and 24-hour urine M protein decreased by 50%-89%. In addition to the criteria listed above, if present at baseline, the size of soft tissue plasmacytomas (SPD) must decrease by ≥50%. |
| **SD** | It is not recommended to use this as a response indicator; the best description of disease stability should be "time to progression estimate." This does not meet the criteria for CR, VGPR, PR, MR, or PD. |

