**International Working Group (IWG) Lymphoma Response Evaluation Criteria (2017)**

|  | **Complete Response（CR）** | **Partial Response（PR）** | **Minor Response（MR）** | **Stable Disease（SD）** | **Progressive Disease（PD）** |
| --- | --- | --- | --- | --- | --- |
| Change from baseline (%) | All target lesions completely disappear, and the longest diameter of all lymph nodes is < 10 mm; | The sum of the longest diameters of target lesions decreases by ≥30% (Partial Response), but does not reach Complete Response; | The sum of the longest diameters of target lesions decreases by ≥10%, but does not reach Partial Response; | The sum of the longest diameters of target lesions decreases by <10% or increases by ≤20%; | The sum of the longest diameters of target lesions increases by >20% |
|  | The sum of the longest diameters of target lesions decreases by ≥30% (Partial Response), while the FDG-PET scan results are normal; |  |  |  |  |
| FDG-PET CT | FDG-PET CT scan results are normal (Deauville score 1 to 3) | FDG-PET CT scan results are positive (Deauville score 4 to 5); | Any FDG-PET CT scan results | Any FDG-PET CT scan results | Any FDG-PET CT scan results |
| Bone marrow involvement | No bone marrow involvement; | Any lesions involving the bone marrow; | Any lesions involving the bone marrow; | Any lesions involving the bone marrow; | Any lesions involving the bone marrow; |
| New lesions | No new lesions. | No new lesions. | No new lesions. | No new lesions. | With or without new lesions. |

*Note: FDG-PET: 18F-fluorodeoxyglucose positron emission tomography.*

Note: ORR =CR+PR+MR; DCR= CR+PR+MR+SD

Reference: Younes A, Hilden P, Coiffier B, et al. International Working Group consensus response evaluation criteria in lymphoma (RECIL 2017) [J]. Annals of Oncology, 2017, 28(7): 1436-1447.

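### ORR is worded as CR+PR, but the operative formulas for lymphoma and myeloma add minor/minimal response (MR), for which no confirmation is stated

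*Protocol*

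**What the plan says.** **Worded definition (Section 7.5).** ORR is the proportion of patients whose tumour has shrunk to a set value that is "maintained for a minimum required duration". It continues: "ORR is generally defined as the sum of complete response (CR) and partial response (PR"). The duration is not quantified there.

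**Operative formulas (table in Section 7.5, repeated in the appendices).**
- Lymphoma, note to Appendix 14.5: "Note: ORR =CR+PR+MR; DCR= CR+PR+MR+SD".
- Myeloma, Section 7.5 table and note to Appendix 14.4: "ORR =sCR+CR+VGPR+PR+MR".
- Acute lymphoblastic leukaemia (ALL): CR+CRi.

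**What an MR is.**
- Lymphoma (Appendix 14.5): "The sum of the longest diameters of target lesions decreases by ≥10%, but does not reach Partial Response". Any PET result and any marrow status are accepted, provided there are no new lesions. PR starts at 30%.
- Myeloma (Appendix 14.4): "Serum M protein decreased by ≥25% but ≤49%, and 24-hour urine M protein decreased by 50%-89" per cent. Soft-tissue plasmacytomas present at baseline must also shrink by at least 50%.

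**Rules that use a PR threshold.**
- The efficacy footnote to the general flowchart asks for confirmation at four weeks "for subjects who first achieve disease remission (CR/PR) after the 2nd, 4th, 6th, etc. dosing cycles".
- The Drug Administration Plan in the Synopsis says that "subjects who achieve an objective response rate of partial response (PR) or higher after 6 cycles may continue receiving the treatment".

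**Analysis.** Section 10.6 calculates ORR with a 95% confidence interval on the FAS. It does not say which definition applies and plans no separate rate at PR or better.

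**The concern.** Most readers take an objective response rate to mean PR or better, and the opening words of Section 7.5 tell them to. The figure produced under the table would be a different one. Take a lymphoma patient whose best result is a 15% fall in summed diameters. That patient is an objective responder under the Section 7.5 table, is not one under the sentence above it, is not covered by the four-week confirmation rule, and is below the level that the Synopsis calls an objective response.

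At stake is how the preliminary efficacy result, a stated secondary purpose in Section 2.2, can be read. Without a separate PR-or-better rate, a reader cannot tell how much of the ORR consists of MRs, and could take an MR-inclusive figure for the CR+PR rate that the text describes.

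**Working it through.** **1. No ORR figure to reproduce.** The protocol states no ORR target, null rate or power. The only related figure is enrolment of 21 to 42 (Section 4.1). It follows from seven dose groups of 3 to 6 subjects: 7 × 3 = 21 and 7 × 6 = 42.

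**2. Does MR count as a response?**

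| Place | Lymphoma | Myeloma |
|---|---|---|
| Section 7.5, worded definition | no | no |
| Section 7.5, table | yes | yes |
| Notes to Appendices 14.5 / 14.4 | yes | yes |
| Flowchart footnote, confirmation | not named | not named |
| Synopsis, objective response after 6 cycles | no | no |
| Section 4.2, response to earlier therapy | no (remission is PR or CR) | yes (MR or better) |

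The last row is why the conflict is stronger in lymphoma. ALL is unaffected, since its ORR has no MR category.

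**3. Size per patient.** Difference = ORR including MR − ORR at PR or better = (number of MR patients) / n.
- n = 42: 1/42 = 2.4 percentage points per MR patient.
- n = 21: 1/21 = 4.8 percentage points per MR patient.

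The FAS also requires a post-baseline efficacy assessment, so n may be smaller than enrolment and each MR patient would then weigh more. The same holds within one disease group.

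**4. Illustration.** The numbers of responders and MR patients below are assumptions. Intervals are exact (Clopper-Pearson) 95%.

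| n | PR or better | MR patients | ORR including MR |
|---|---|---|---|
| 42 | 8 (19.0%; 8.6–34.1) | 2 | 10/42 = 23.8% (12.1–39.5) |
| 42 | 8 | 4 | 12/42 = 28.6% (15.7–44.6) |
| 42 | 8 | 8 | 16/42 = 38.1% (23.6–54.4) |
| 21 | 4 (19.0%; 5.4–41.9) | 1 | 5/21 = 23.8% (8.2–47.2) |
| 21 | 4 | 2 | 6/21 = 28.6% (11.3–52.2) |
| 21 | 4 | 4 | 8/21 = 38.1% (18.1–61.6) |

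**5. How easily could measurement error alone cross the lymphoma threshold?** The documents give no measurement error, so this is illustrative only. Assume that the true tumour size is unchanged and that the measured percent change is normal with mean 0 and standard deviation s. Then P(one reading at or below −10%) = Φ(−10/s), and P(at or below −30%) = Φ(−30/s).

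| s (assumed) | at or below −10% | at or below −30% |
|---|---|---|
| 5% | 2.3% | <0.01% |
| 8% | 10.6% | 0.01% |
| 10% | 15.9% | 0.1% |
| 15% | 25.3% | 2.3% |

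Taking the best of several readings raises these figures; requiring the fall to persist lowers them. They show only that the 10% threshold is more exposed to error than the 30% threshold, which is where a confirmation rule would help most.

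**The case against.** The strongest reply is that the operative definition is not in doubt. The CR+PR sentence is softened by the word generally. The table is introduced as the correspondence for this trial, and both appendices repeat its formulas. The MR-inclusive ORR is therefore prespecified and consistent, and this part stands: nobody following the table would be making a hidden change. But prespecifying a formula does not reconcile it with the definition printed above it or with the PR-based rules elsewhere.

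Other points that stand:
- The confirmation footnote speaks of remission and does not name sCR, VGPR or CRi either, so it may be shorthand. The Synopsis passage concerns treatment continuation and is not an endpoint definition.
- In myeloma, Section 4.2 accepts MR as a response to earlier therapy, and MR is more demanding than a 25% serum fall alone: the urine criterion and, where relevant, the plasmacytoma criterion also apply.

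A reader might also infer more than the documents support:
- *That unchanged tumours will often be counted as responses.* This depends wholly on an assumed measurement error and on ignoring the worded requirement that the decrease be maintained.
- *That an MR is never looked at again.* Imaging recurs every two cycles during extended treatment. What is missing is a stated confirmation of MR.
- *That one pooled ORR will mix a 10% shrinkage with complete remission of leukaemia.* Section 10.6 does not say that diseases are pooled, and Section 10.8 leaves detailed methods to the SAP.
- *That Phase II dosing would be distorted.* Section 2.1 rests the dosing regimen on DLT and MTD. No decision rule uses ORR.

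**Conclusion.** The point holds as an internal contradiction with a known direction. For lymphoma and myeloma, the ORR calculated from the table is at least as high as the CR+PR-type rate described in the same section, and higher as soon as one patient has MR as best response. The excess is the MR share, 2.4 points per MR patient at n=42 and 4.8 at n=21. Its total is unknown because the protocol gives no MR rate; the 23.8% to 38.1% range in the illustration rests on assumed counts. The excess is measured against the protocol's own wording, not against an outside standard.

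The weight is moderate. The case is clearest in lymphoma and weaker in myeloma, and ALL is untouched. ORR is a secondary, descriptive endpoint, so neither type I error nor sample size is affected. Correction is worthwhile because it is cheap and makes the efficacy result readable.

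**What to change.** In Section 7.5 and the notes to Appendices 14.4 and 14.5:
1. Label the PR-or-better rate as ORR: lymphoma CR+PR; myeloma sCR+CR+VGPR+PR; ALL CR+CRi, unchanged.
2. Report MR as its own row, and keep the prespecified MR-inclusive rate as a supportive rate under its own name, such as MR or better.
3. Keep MR in the lymphoma DCR.
4. Report these rates by disease group.

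Reconcile the efficacy definition with the wording of the continuation passage in the Synopsis, so that objective response has one meaning throughout. That is a matter of terminology; which clinical rule should govern continuation is not for this review.

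If the sponsor prefers to keep MR within ORR, the minimum is to correct the opening sentence of Section 7.5, state how an MR is confirmed, and report the PR-or-better rate beside it.

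The preferred change is wording only and uses response categories already collected. Its price is a somewhat lower headline ORR.

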# Adverse Events and Serious Adverse Events

## Adverse Events

### Definition

Adverse Events (AEs) refer to any unfavorable medical occurrences experienced by a patient or clinical trial subject after receiving a medication, but they do not necessarily have a causal relationship with the treatment. An adverse event can include any unfavorable and unintended sign (including abnormal laboratory findings), symptom, or disease that occurs in temporal relation to the use of the investigational drug, regardless of whether it is related to the drug. This includes, but is not limited to:

1. Worsening of pre-existing conditions prior to the use of the investigational drug;
2. Increased frequency or severity of pre-existing episodic events prior to the use of the investigational drug;
3. Abnormal changes detected or diagnosed after the use of the investigational drug, even if these changes may have existed prior to treatment;
4. Deterioration of diseases or symptoms that were already persistently present before the start of the study.

